#### Study location and participant demographics.

Participants will be recruited from the undergraduate student population at Ulster University, Coleraine, Northern Ireland, UK and all study visits will take place at the Centre for Optometry and Vision Science at Ulster University. An undergraduate student population has been chosen as an appropriate homogenous population to trial coloured spectacle lenses, as it is expected that this cohort will spend greater periods of time reading than the general adult population. Therefore, any potential benefit of a precision tint can be trialled in a population who will engage heavily with reading material.

#### Inclusion criteria.

All participants shall be adult undergraduate students at Ulster University, aged 18–45-years. Participants shall be recruited in their first year of their current university degree. It is anticipated that the majority of participants will be young adults between the ages of 18–25, owing to the high prevalence of this age cohort attending undergraduate lectures. All included participants will be pre-presbyopic, i.e., not requiring a specific refractive error addition for near vision tasks/reading. Participants will be enrolled in the trial on the basis of presence of symptoms suggestive of visual stress, as determined by a reading symptom questionnaire and as detailed in Table 1.

**Table 1 pone.0309625.t001:** Recruitment criteria used to determine presence of visual stress.

Participants must satisfy at least one of the following sets of inclusion criteria:	
1. Presence of Significant Symptoms and Pattern Glare	Presence of any two symptoms with frequency scores ≥3, from the following: ‘Words/ letters look jumbled’. ‘Patterns seen in the white spaces between words/ letters’. Colours in the white spaces between words/ letters’. ‘Repeating words/ lines of text’. ‘Skipping words/ lines of text’. ‘Losing your place when reading’. ‘Words/ letters flicker when reading’. ‘Shimmering over the words/letters’. ‘Words/ letters wobble when reading’. ‘Words/ letters move’. ‘Words/ letters merge’. ‘Patterns/ shadows seen in text, e.g., rivers’. ‘Letters/ words stand out in 3D above the page’. ‘Letters/ words fade or darken on the page’. AND a pattern glare test score >3
2. Total Symptom Score >50%:	Summed total Likert symptom frequency score of 14-symptoms from 0-5 exceeds a 50% total score threshold (>35/70), when excluding 3 of the 17 Likert symptoms listed in the questionnaire, which may differentially diagnose other ocular abnormality (listed in brackets), which are: ‘Headaches when reading’. (Headache) ‘Eyestrain when reading’. (Asthenopia) ‘Words/ letters look blurred’. (Uncorrected Refractive Error)

#### Exclusion criteria.

Participants will be excluded if they satisfy any one of the following criteria:

Habitual distance monocular acuity poorer than 0.1 logMAR.Habitual near monocular acuity poorer than N5 at 40 cm.Presence of manifest strabismus and/or decompensating phoria observed on alternating cover test.Near point of convergence greater than 10 cm.Failure to meet Duane-Hoffstetter Criteria for minimum binocular push-up accommodative amplitude (>15-[0.25]*[age in years]) – see Monger et al. [32]Absence of observable stereopsis on the Randot stereotest.Formal diagnosis of photosensitive epilepsy

Diagnosis of photosensitive epilepsy will form an exclusion criterion owing to the epileptogenic nature of the repeated striped patterns of the mid-spatial frequency ‘pattern 2’, of the pattern glare test, as detailed in the tests instructions [33].

Those diagnosed with dyslexia and/or other specific learning disability (SpLD) will not be excluded from the trial owing to the concurrence of these conditions and visual stress [5], and differences in the symptom profiles and diagnostic criteria used to determine presence of reading difficulty. Irrespective of dyslexia/SpLD diagnosis, researchers will assume presence of VS in all identified participants on the basis of diagnosable pattern glare, concurrent with reported visuoperceptual reading symptoms, as detailed in Table 1. Data on profile of SpLD/dyslexia diagnosis of participants will be available to researchers after trial completion and may be considered in post-hoc analysis of coloured lens efficacy.

Further binocular vision tests which will be conducted at baseline, but are not used as exclusion criteria for the clinical trial include: fusional reserves (positive, negative and vertical); near associated phoria; accommodative facility; dynamic retinoscopy and calculation of the AC/A ratio.

### Recruitment

#### Reading symptoms screening.

A reading symptom questionnaire was developed to screen large cohorts of undergraduate students in lecture theatres (see Supporting Information S2 File). There are currently no validated criteria used to diagnose visual stress [1,3]. Therefore, reading symptoms employed in the questionnaire were devised from symptoms of visual stress reported in the literature such as those proposed by a Delphi study [3] and the ‘Visual Stress Index’ [6]. The questionnaire includes 17-items and 6-point Likert scale with descriptors of symptom frequency (0 = never; 5 = always). Participants will be directed to consider their reading symptoms on a day-to-day basis when completing the questionnaire. Additionally, participants will be provided with a sample of crowded text in a foreign language, devoid of context, to consider when answering the questionnaire, if they are uncertain about the explanation of a particular reading symptom [6].

Questionnaire test-retest reliability was assessed on a sub-group of 115-undergraduate students through repeat issuing of the questionnaire six weeks after initial screening. Participants were blinded to motivation for retesting. High intraclass correlation coefficients were noted (0.91), with low bias of −1.99 (change in symptom scores with repeat measures, with a negative value indicating an increase on total summed symptom score on repeat) by Bland-Altman analysis [34]. Overall questionnaire internal consistency was also considered high by Cronbach’s alpha (α = 0.92) calculations. These findings confirm overall questionnaire test-retest acceptability for screening purposes.

Further questions exploring participants’ ocular and general health will be posed, as well as questions investigating presence of potential visual stress co-morbidities such as; headache [35,36]; formal diagnosis of migraine [37–40]; diagnosis of dyslexia [5,41,42] and/or diagnosis of specific learning difficulties and other general health complaints, known to also be managed with coloured filters [17,43–45].

To determine presence of cortical hyperexcitability, a mid-spatial frequency pattern glare test will also be administered. A 40 cm string will be affixed to the test, to measure the proposed viewing distance of ‘pattern 2’ of the pattern glare test series (spatial frequency 2.3cpd) [33]. Respondents will be directed to circle ‘yes/no’ responses to each of the seven pattern glare symptoms as per the test instructions [33,46]. Each positive ‘yes’ response will be summed to determine a total pattern glare score ranging from 0-7.

Reading symptom questionnaires will be administered during term time. The researchers will attend lecture theatres and inform students that they are conducting an investigation of symptoms students experience whilst reading. Recruitment to this study began on 08/12/2022. Repeat rounds of screening will be conducted year-on-year with newly enrolling first-year undergraduate students, if initial recruitment is sub-optimal. It is anticipated that final recruitment will be completed by 20/12/24. Participants will be informed that completion of the questionnaire is voluntary and that all information disclosed will be treated confidentially. Participants will not be informed of the potential to participate in the randomised control trial until after completion of the questionnaire to avoid biasing results.

#### Determination of the presence of visual stress.

In the absence of standardised diagnostic criteria for visual stress, recruitment criteria were devised on the basis of previously reported criteria and methods of recruitment to previous investigations within the literature [5,11,12]. One drawback of previous investigations of coloured filter efficacy is the inability of some studies to accurately determine presence of visual stress in participants, with some incorrectly enrolling participants on the basis of dyslexia diagnosis [47–49] or due to variations in definition of visual stress symptoms (see review by Griffiths et. al. 2016) [1]. The current study will employ strict recruitment criteria to ensure that the most symptomatic individuals are included in the study. Participants who satisfy at least one set of the inclusion criteria as listed in Table 1 shall be invited to take part in the trial. By satisfying either criterion, participants will be recruited on the basis of (i) presence of pattern glare and at least two significant visuoperceptual reading symptoms indicative of visual stress or (ii) overall summed symptom severity across an array of 14-visuoperceptual symptoms.

### Procedure

#### Interventions employed (determination of control lens).

The ‘Curve’ Intuitive Colorimeter ™ [50] will be used to determine chromaticity of ‘experimental’ (optimal) and ‘control’ (sub-optimal) tints, through manipulation of the hue, saturation and luminance of a projected series of three primary colours to comprise a gamut of visible chromaticities spaced throughout the 1976 CIELUV colour space [51,52].

Participants will identify an ‘experimental’ tint through a series of repeated presentations of opposing hues. Initially, 12-predetermined hues, separated by a ‘hue angle’ of 30˚ will be presented. Participants will compare the appearance and comfort of a random series of letters forming a striped body of text devoid of context within the Intuitive Colorimeter™, illuminated under white light and presented hue. Participants will note if the presented hue makes the appearance and comfort of the crowded text ‘better’, ‘worse’ or ‘no-different’ than white-light. Beneficial hues will be shortlisted. Saturation of each shortlisted hue will be reduced until symptoms arise. Saturation will then be adjusted to the lowest level where symptoms resolve. A 2-alternative forced choice of preferred hue of ideal saturation will then be presented until an optimal chromaticity can be determined, as previously described [53]. Once optimal hue and saturation are determined, luminance will be attenuated between ‘half’ and ‘full’ settings and the participant offered a preference choice. An arc of beneficial therapeutic colours will be uncovered through this technique. This area of therapeutic chromaticities will represent an area on the 1976 CIELUV colour space wherein observers are expected to derive benefit from colour. The authors propose that variation in size and location of this therapeutic region will exist amongst observers. Boundaries of the colour space will be denoted as two ‘hue angles’ on the Intuitive Colorimeter™ colour wheel, outside which therapeutic benefit is lost. Optimal chromaticity will lie within this colour space. This arc of beneficial chromaticities will be herein referred to as the ‘Limit of Therapeutic Effect’.

The ‘control’ lens will act as the placebo and will be sub-optimal, when compared to ‘experimental’ tint. To determine control tint, researchers will prescribe a colour that will not be aversive, yet not beneficial to the patient’s symptoms of visual stress that lies just outside the ‘Limit of Therapeutic Effect’. At the upper and lower boundary of the Limit of Therapeutic Effect, participants will consider if reading symptoms/ visual discomfort experienced are ‘worse’ or ‘no different’ compared no colour presented. The hue will be adjusted to when participants confirm that there is ‘no difference’ when compared to no colour (i.e., not beneficial nor aversive). At these two hues, the researchers propose that these are the candidate control tints. The control tint chosen will be that closest to the optimal tint on the colour diagram, to assist with participant masking – i.e., the apparent colour difference will be more visually alike between control and optimal tint. ‘Control’ tint will be of the same saturation and luminance to the ‘experimental’ tint. Researchers are mindful of previous work, stating inter-practitioner and inter-instrumental measurement error may account for ~0.03 units of chromaticity difference (the Euclidean distance between colour coordinates mapped on the 1976 CIELUV Chromaticity Diagram) between lenses [54,55]. Whilst a consistent chromatic separation between lenses will not be applied, to account for assumed difference in size of ‘Limit of Therapeutic Effect’ by observers, size of chromatic separation between lenses will be considered in post-hoc analysis of reading performance. The authors appreciate that there is a certain degree of variability in determining sub-optimal tint by this method, as demonstrated in work by Suttle and colleagues (2017) [56], whereby number of just noticeable differences between precision tints varied between 23.8 and 3.1, among 21 observers. However, researchers will aim to ensure that the ‘control’ tint be inert, through confirmation of participants’ visuoperceptual symptoms when viewing the striped body of text within the Intuitive Colorimeter™ illuminated by the assumed ‘control’ chromaticity. Furthermore, the chromaticity difference, between colour coordinates of ‘experimental’ and ‘control’ lenses will be measured by the Mark 2 SpectroCAL Spectroradiometer (Cambridge Research Systems Ltd., Cambridge, UK). Chromaticity coordinates will be plotted by computer software (Light Values Measuring System, Version 6.2.0, Windows 11.0 OS, Jeti Technische Instrumente GmbH [name], Jena, Germany). Chromaticity difference between ‘experimental’ and ‘control’ tints will be considered in post-hoc analysis of reading performance with the use of coloured lenses.

Additionally, participants will be graded on their ability to decipher beneficial therapeutic colour and will be classified as ‘good’, ‘moderate’ or ‘poor’ observers in line with previous investigations [55]. Individual descriptors are detailed in Table 2 below. If a participant is unable to derive benefit from any precision tint, they will be excluded from the clinical trial.

**Table 2 pone.0309625.t002:** Grading scales of participants’ responses on the intuitive colorimeter™ adapted from Aldrich et al (2018) [55].

Grading	Description
Good	Participant identifies an optimal colour and does not deviate
Moderate	Participant identifies a colour with only minimal adjustment
Poor	Participant is unsure and/or colour is repeatedly adjusted

#### Randomisation and blinding.

Randomisation of interventions will be conducted by the Ulster University School of Biomedical Sciences’ Clinical Trials Manager. As participant recruitment will be conducted on an ongoing basis, interventions will be randomised on a simple 1:1 basis without stratification, to ensure that if subpar enrolment is achieved, an equal number of participants will be engaged with each intervention at each timepoint in the trial. Therefore, approximately half of participants will initially receive the optimal tint whilst the other half will firstly receive the sub-optimal tint. Researchers and participants will be blinded as to which lenses are assigned throughout the duration of the trial. Both spectacle frames housing the spectacle lenses will be identical to mask researchers and participants to the intervention employed.

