## Methods and materials

### Study design

This study is designed as a double-masked cross-over randomised placebo-controlled trial of coloured lens efficacy in adults with symptoms of visual stress. The trial design is supported by the Standard Protocol Items: Recommendations for Intervention Trials (SPIRIT) framework (see supporting information S1 File). Participants will be evenly and randomly assigned one of two sets of coloured spectacle lenses for initial spectacle wear for a period of six weeks, followed by wear of an alternate pair of spectacle lenses for a further six weeks. Coloured spectacle lenses will differ in their chromaticity, with the ‘experimental’ coloured lenses, tinted to optimal chromaticity, which are presumed to reduce perceptual distortion symptoms, whilst ‘control’ lenses will comprise a chromaticity similar in perceptual colour appearance to ‘experimental’ lenses, to assist with masking, but differing in chromaticity, such that visual stress symptoms are neither improved nor worsened with use of tint. The ‘Control’ lenses shall therefore act as a placebo. Researchers and participants will both be masked to the spectacle lenses worn. A two week washout between periods of spectacle lens wear will be employed, so that any potential legacy effects of coloured lenses are negated.

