### Study population

#### Sample size calculation.

The Wilkins Rate of Reading Test reading speed has been used as the outcome measure for an improvement with use of coloured filters [12,13,28–31]. Sample size was calculated using statistical software (G-Power, Version 3.19.4, 2024), for an a priori within-factors repeated measures ANOVA of the Wilkins Rate of Reading Test (the primary outcome measure of this trial). A partial eta squared (${\eta \rho }^{2}$) of 0.0355 was used with a conservative small to medium effect size (f) of 0.1985. Probability of a type-1 error (α), of 0.05 and power (1−β) of 0.90 were applied. Correlation among repeat measures was assumed 0.5 and nonsphericity correction (ϵ) was held at 1.0. A sample size of 59 participants was determined appropriate for this investigation The required sample size has been increased by 10% to account for attrition. Therefore, 65 participants shall be recruited for the trial.

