### Trial progress to date

1071 undergraduates at Ulster University have been screened for symptoms of visual stress, 171 undergraduates have met recruitment criteria and have been invited to participate in the trial. 60 participants are currently enrolled in the trial. Researchers plan to screen newly enrolled undergraduate students at the start of the 2024−25 academic year, to ensure adequate trial enrolment.

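### Simple 1:1 randomisation cannot ensure equal numbers on each lens in each period, and the named primary analysis has no period term to absorb the imbalance it leaves

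*Protocol article*

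**What the plan says.** Under Randomisation and blinding the protocol article says that "interventions will be randomised on a simple 1:1 basis without stratification, to ensure that if subpar enrolment is achieved, an equal number of participants" would wear each lens at each timepoint. The following sentence promises less: "approximately half of participants will initially receive the optimal tint whilst the other half will firstly receive the sub-optimal tint". Study design uses the stronger sense again: "Participants will be evenly and randomly assigned one of two sets of coloured spectacle lenses". The article describes no blocking, minimisation or other restriction.

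Under Statistical analyses the primary outcome, reading speed on the Wilkins Rate of Reading Test (WRRT), is to be analysed by repeated measures ANOVA for both lenses at baseline, at spectacle collection and after six weeks of wear. The post-hoc ANCOVA covariates are baseline speed, reading errors, days and hours of wear, and hours of concentrated tasks. Neither period nor sequence is named in either analysis. The washout is justified by carryover only.

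The target is 65 participants. Under Trial progress to date, "60 participants are currently enrolled in the trial".

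**The concern.** The stated method does not have the stated property. Under simple randomisation each participant's sequence is an independent coin toss. The split is therefore equal only in expectation, and relative imbalance grows as numbers fall. Poor enrolment, the situation given as the reason for the choice, is where the method does worst.

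This matters because the trial is a two-period crossover. Equal sequence groups are what cancel a period effect out of an unadjusted lens comparison. A period effect is plausible here. The WRRT repeats the same 15 words, is read twice per visit and is used throughout the trial. The protocol guards against learning on the Adult Reading Test by alternating passages, but describes no such step for the WRRT. If the sequences are unequal and the model has no period term, part of any practice gain is credited to the lens more often worn second.

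**Working it through.** **Inputs from the protocol.** Allocation is simple and 1:1. N = 59 evaluable and 65 recruited (Sample size calculation); 60 are enrolled (Trial progress to date). Alpha is 0.05. The period effect is not given, so it is treated as an assumption, with a range shown.

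**1. The plan's own N.** Partial eta squared of 0.0355 gives f = sqrt(0.0355/0.9645) = 0.1919. With three repeated measures (the number in the analysis section), correlation 0.5, epsilon 1 and alpha 0.05, the noncentral F calculation gives N = 59 at power 0.901. Then 59 x 1.10 = 64.9, so 65. The plan's N is reproduced. (The printed f of 0.1985 would give 56; that mismatch is a separate matter.) The plan gives no figure for balance, so there is none to reproduce.

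**2. How often simple randomisation delivers balance.** The number starting on the experimental lens is Binomial(N, 0.5).

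| N | Exact or nearest split | Probability | Mean absolute difference |
|---|---|---|---|
| 59 | 30/29 | 0.205 | 6.2 |
| 60 | 30/30 | 0.103 | 6.2 |
| 65 | 33/32 | 0.196 | 6.5 |

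- At N = 60: P(33/27 or worse) = 0.519 and P(35/25 or worse) = 0.245.
- At N = 65: the median difference is 5, P(37/28 or worse) = 0.321 and P(41/24 or worse) = 0.046.
- The standard deviation of (n1 - n2)/N is 1/sqrt(N): 0.124 at 65, 0.129 at 60 and, if enrolment had stopped at an illustrative 30, 0.183.

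**3. Effect on an unadjusted lens contrast.** Let t be the lens effect and p the period effect (period 2 minus period 1). The within-person difference, experimental minus control, has mean t - p if the experimental lens is worn first and t + p if it is worn second. Averaged over N participants, the contrast is shifted by p x (n1 - n2)/N, where n1 is the number wearing the experimental lens second.

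- N = 65, median imbalance: 5/65 = 8% of p
- N = 65, 37/28: 9/65 = 14% of p
- N = 65, 41/24: 17/65 = 26% of p
- N = 60, 33/27: 6/60 = 10% of p

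On an assumed scale of p = 2%, 5% or 10% of reading speed, a 33/27 split shifts the contrast by 0.2, 0.5 or 1.0 percentage points. The protocol's lowest improvement category starts above 5%.

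**4. Behaviour over the randomisation and for a fixed split.** This was simulated at N = 65 with no lens effect and p in units of the SD of the within-person lens difference (assumed 0 to 1).

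- Simple randomisation, no period term: mean bias about 0 and type I error 4.8% to 5.1% for every p tried. The SD of the estimate is 0.138 at p = 0.5 and 0.175 at p = 1. As a check, sqrt((1 + p^2)/65) gives 0.139 and 0.175.
- Simple randomisation, period term included: mean bias about 0, SD about 0.125, type I error about 5%.
- Fixed split, p = 0.5, no period term: at 37/28 the shift is 0.07 SD and type I error 5.4%; at 41/24 they are 0.13 SD and 12.8%. With a period term the shift vanishes and type I error is about 5% in both cases.
- Balanced 33/32 without a period term: type I error is 4.1%, 2.7% and 0.6% at p = 0.25, 0.5 and 1. The test is conservative because period variation stays in the error term.

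**5. Cost of imbalance once period is fitted.** Variance is multiplied by N^2/(4 n1 n2). At 33/27 this is 3600/3564 = 1.010; at 37/28 it is 4225/4144 = 1.020.

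**The case against.** The stronger reading is that simple randomisation without a period term biases the trial or inflates its type I error. The documents do not support it. Over the randomisation the unadjusted estimate is centred correctly and the test holds about 5%. A shift exists only given a realised imbalance and a non-zero period effect, and the documents report neither. The 12.8% above needs an assumed period effect of 0.5 SD and a split of 41/24, and a split that uneven or worse has probability 0.046.

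Other points in the plan's favour have weight:

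- Every completer wears both lenses, so total exposure is balanced. Only the numbers per period can differ.
- The word simple may be loose wording for an unstratified balanced list, which would fit the wording in Study design. The full protocol is not shown and may name blocks.
- Model terms are often left to an analysis plan, and the article does not spell out the exact lens contrast, so how far a period effect enters cannot be settled from the text.
- The article rates the learning risk of another random-order test, the Developmental Eye Movement test, as low. A reader could extend that to the WRRT.
- With 60 of 65 enrolled, early stopping is largely overtaken, and blocking about five allocations cannot undo an imbalance built up over 60.

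These limit the size of the problem and move the remedy from allocation to the model. They do not rescue the sentence: either the method is misnamed or the property claimed for it is false. The article does list its analysis and covariates, and period is in neither list.

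**Conclusion.** The point stands in a limited form. The claim that simple 1:1 randomisation ensures equal numbers at each timepoint is wrong as stated, and the section's own next sentence retreats to an approximate split. In trials of this size the promised balance, or the nearest to it, would be missed about 80% to 90% of the time.

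With the analysis as named, the consequence is lost precision on average and a chance shift in the trial actually run, most often a small fraction of the period effect. This assumes that allocation really was unrestricted, that the lens contrast is the unadjusted within-person one, and that a period effect exists. If there is none, the imbalance costs almost nothing.

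**What to change.** 1. In Randomisation and blinding, delete the claim that simple randomisation ensures equal numbers. If the list was in fact restricted, name the method instead. Bring the wording in Study design into line.
2. In Statistical analyses, include period, with sequence, as fixed terms in the primary WRRT comparison of experimental and control lenses, and record this before unmasking. The period term does the main work: it removes the shift whatever the split, including imbalance from dropout, which no allocation method prevents.
3. Report the number allocated to and completing each sequence.

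The cost is a corrected sentence and two model terms. Permuted blocks for the remaining allocations are optional and would have little effect. Blocking without a period term would not be a sufficient remedy, since the test would then be conservative whenever a period effect exists.
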